### The intervention and its delivery

2.6

In this study, participants will be offered the Triple P Positive Parenting Program for Baby (11, 30–32, 69), which aims to increase parenting skills and confidence in parents of infants (up to 12 months) by targeting the parent-baby bond, increasing the parent’s understanding of infant development, responding to the baby’s cues in a way that supports infant mental health and learning to communicate effectively with the partner/co-parent or another family member. All participants will be offered access to the self-paced Triple P for Baby Online intervention, with content offered in seven brief sessions, which are accessed online as a series of videos featuring parents discussing their experiences of various aspects of parenting in the first year and a narrator sharing factual information about infant development and parenting (see **Table 1** for details).

**Table 1 T1:** Overview of the triple for baby online intervention structure and content.

Session number	Session title	Session content
1	Positive parenting	Provides parents with an introduction to positive parenting as an approach to raising infants, factors that have an impact on early child development, and specific parenting strategies for developing a positive relationship with their baby.
2	Understanding your baby’s development	Parents are introduced to elements that can play a role in their baby’s development and ways they can monitor and keep track of their baby’s behaviour and development.
3	Developing a positive relationship	Parents learn strategies for developing a positive relationship with their baby and how to teach their baby new skills and behaviours.
4	Responding to your baby	Parents are helped to understand crying and teach settling techniques. Parents will also learn how to apply parenting strategies to promote positive sleeping habits.
5	Survival skills	Parents are introduced to changes new parents may experience, some of the early parenting traps, and a variety of coping strategies to manage emotions (e.g., stress, anxiety, sadness).
6	Partner support	Provides parents with information on common relationship changes new parents may experience and some partner traps. The importance of communication and ideas for maintaining relationship happiness are also introduced.
7	Conclusion	Parents are encouraged to think about how to implement the skills and knowledge they have learnt during the programme in the future.

After completion of the baseline measures, the research team will provide participants with a link to register for Triple P for Baby Online. Following registration, participants will have 12 months of access to the intervention via an internet−connected device (e.g., laptop, smartphone, or tablet), at a location and time of their choice. Participants will be asked and encouraged to complete all seven sessions of the intervention within ten weeks (a timeframe chosen to account for busy perinatal periods). Participants’ care and treatment from the specialist perinatal service will continue as usual while they take part in the study; this care might include care-coordination and psychological interventions (e.g., compassion-focused therapy, cognitive behavioural therapy, eye movement desensitisation and reprocessing therapy, dialectical behaviour therapy, cognitive analytic therapy, delivered individually or as part of an online group intervention).

To support and maximise engagement and answer any questions the mother may have about the intervention, study staff will offer encouraging prompts via text messages and brief phone calls to check on their progress (prior to session 1 to help with access, then after sessions 1, 3 and 5). These phone calls will also act as ‘trouble shooting’ support for any technical or comprehension issues and they will also enable the research team to check for any adverse events.

### Feasibility outcomes

2.7

Feasibility will be assessed by examining data related to recruitment and study retention (i.e. completion of outcome measures at follow up). To evaluate the suitability of this study to progress to a larger, randomised trial, we will use the red, amber, green (RAG) system and pre-determined progression criteria (70–72). **Table 2** provides an overview of our proposed progression criteria. We will also report on a range of feasibility indicators (e.g., number of potential participants found to be eligible, reasons for declining to participate, the extent and pattern of missing data, the number of related adverse events, etc.). In addition, the Triple P Online Management system will allow the research team to monitor participants’ progress through the programme and aggregate relevant feasibility data on engagement (e.g., how many and what sessions were completed, dates of first and last log-ins, number of log-ins per participant).

**Table 2 T2:** Progression criteria for feasibility.

Indicator	Green	Amber	Red
Recruitment: number of eligible participants recruited within our recruitment window of 29 weeks	≥ 60% = green	50–59% = amber	≤ 49% = red
Study retention: proportion of participants completing measures at each data collection point (baseline and follow up)	≥70%	50-69%	≤49%

### Acceptability outcomes

2.8

Intervention acceptability will be assessed quantitatively via the Client Satisfaction Questionnaire (73), administered to participants at follow up via the online survey tool, Qualtrics. Participants will be asked to answer 13 questions (rated on a 7-point Likert scale) and three open-ended questions (e.g., Do you have any other comments about the programme)?.

Qualitative exploration of acceptability will be conducted via online interviews with a sub-group of participants and staff. Acceptability in this context will focus on the exploration of attitude towards the intervention, intervention and assessment burden, and facilitators and barriers towards uptake and engagement with the intervention, as informed by Sekhon et al.’s (74) theoretical framework of acceptability.

Separate consent for this aspect of the study will be sought. Interviews will explore participants’ views of the intervention content, mode of delivery, the encouraging phone calls and text messages, and the study procedures, such as assessment burden. We will also conduct exit interviews with mothers who withdraw from the study, if possible.

### Questionnaire outcomes

2.9

At baseline, mothers will be asked to complete the Family Background Questionnaire (75), adapted for perinatal populations, which will ask for details of their ethnicity, the age and sex of their baby, family and household composition, their marital and employment status and brief details about characteristics and experiences that may predict attrition and outcome, such as psychiatric history, educational attainment and family support. The type and duration of standard care that mothers have received while participating in the study will be recorded to report what other treatments mothers (or birthing parents) were offered and then accessed; this will test the feasibility of using Treatment As Usual (TAU) as a comparative arm for a future trial.

Participants will also be asked to complete four brief validated questionnaires assessing mood (i.e., depression, anxiety, stress), wellbeing, maternal self-efficacy and the perceived mother-infant bond, chosen for their relevance, their psychometric properties and widespread use in related research (see **Table 3** for further details). They will be asked to complete these questionnaires via the online survey tool, Qualtrics, either on their own or with the support of a researcher over a telephone or video call on Microsoft Teams. At follow up (i.e., 10–12 weeks post-baseline), participants will be reminded to complete the same four questionnaires. At the same time, we will also ask them to complete the Client Satisfaction Questionnaire (73). The assessments are anticipated to take up to 30 minutes to complete. **Figure 2** provides an overview of all study data collection points.

**Table 3 T3:** Overview of outcome questionnaires used.

Number	Outcome measure	Rationale	Item numbers and subscales	Scale type	Scoring range (minimum and maximum scores) and interpretation	Psychometric properties
1	Depression, Anxiety and Stress Scale-21 (DASS-21; 76)	To measures levels of depression, anxiety and stress	21 items: *Depression (7) *Anxiety (7) * Stress (7)	4- point Likert scale	0-21 (for each subscale) Higher the score indicates the more severe the symptoms	Cronbach’s alpha-.76-.93 Test-retest reliability- ICC = .82 -.86
2	Short Warwick Edinburgh Mental Wellbeing Scale (SWEMWBS; 77)	To measure well-being	7 items	5-point Likert scale	7-35 Scoring 7 to 35 (minimum/maximum scores) Higher scores indicate lower well-being	Cronbach’s alpha-.88-.93 Test-retest reliability- r = .86
3	Maternal Efficacy Questionnaire (MEQ; 78)^1^	To measure of parental self-efficacy	20 items: *Care taking procedures (5) *Evoking behaviours (5) *Reading behaviours (5) *Situational beliefs (5)	4-point Likert scale	20-80 (Minimum/maximum scores) Higher scores indicate higher maternal self-efficacy	Cronbach’s alpha-.91 Test-retest reliability- r= .96
4	Postpartum Bonding Questionnaire (PBQ; 79)^2^	Measures the difficulties in parent and infant bond	25 items: *Impaired bonding (PBQ-IB) (12) *Rejection and anger (PBQ-RA) (7) *Infant- focused anxiety (PBQ-IFA) (4) *Incident abuse (PBQ-LA) (2)	5-point Likert scale	0-125 (minimum/maximum) PBQ-IB: 0-60 PBQ-RA: 0-35 PBQ-IFA: 0-20 PBQ-LA: 0-10 Higher scores indicate higher perceived bonding difficulty	Cronbach’s alpha-.78-.79 Test-retest reliability- r = .77-

^1^Pregnant participants are not asked to complete this measure.

^2^An adapted version is available for pregnant women.

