### Data analysis

2.11

Participant flow through the study will be reported using the CONSORT diagram (**Figure 1**). Descriptive summaries will be produced for feasibility and other outcome data (e.g., means and standard deviations or numbers and percentages, including percentages and patterns of missing data). We will use a paired t-test or Wilcoxon signed rank test for pre- and post-intervention questionnaire data and the reliable change index (80, 81) to explore changes in clinical outcomes (i.e., potential intervention benefits). However, given that this is an uncontrolled study, any results in relation to outcomes will be treated with extreme caution.

All interview data will be digitally recorded, transcribed verbatim and then analysed using Framework Analysis (82, 83). Informed by the acceptability of healthcare interventions theoretical framework (74), an initial coding framework will be developed to reflect key service and service user-determined topics covered by the interview schedule. Following data familiarisation, this framework will be augmented to encompass new emerging themes. Initially, a subset of transcripts will be coded independently by a member of the research team, and findings will be discussed by the rest of the research team and the PPIE group to develop a shared theoretical framework. This framework will then be applied to the remaining transcripts. Data will be interpreted and analysed within the final framework to structure and compare participant and staff views about the study and intervention. The trustworthiness of the final analysis will be enhanced through the integration of data from different stakeholders and through researcher triangulation.

Given the small-scale uncontrolled nature of this trial, a data monitoring committee was not deemed necessary. Instead, the research team conducted monthly trial monitoring meetings, and the project managers regularly conducted a review of trial documents.

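### Table 3 gives the SWEMWBS a direction that contradicts the row's own purpose; if followed, reliable improvement and reliable deterioration in wellbeing swap

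*Protocol article*

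**What the plan says.** Wellbeing is a named outcome in the abstract, in the aims at the end of the Introduction and in section 2.9. It is measured by the SWEMWBS, the second row of Table 3. That row gives the rationale as "To measure well-being", lists seven items on a "5-point Likert scale" and reports "Test-retest reliability- r = .86". The column for score range and interpretation gives 7 to 35 and then reads "Higher scores indicate lower well-being".

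Section 2.11 plans a paired t-test or Wilcoxon signed rank test on the pre- and post-intervention questionnaires, together with the reliable change index, "to explore changes in clinical outcomes (i.e., potential intervention benefits"). It adds that outcome results will be read very cautiously because there is no control group.

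Nowhere does the article mention reverse scoring or recoding of the SWEMWBS, and no other section gives the opposite direction.

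**The concern.** A score introduced as a measure of wellbeing should rise as wellbeing rises, unless the authors say it has been reversed. The row says the opposite and gives no reason.

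Direction is a required input for the reliable change index, which sorts each woman into improved, unchanged or deteriorated. It also fixes how the sign of the mean change is read. With the direction reversed, a woman whose wellbeing rose would be labelled as worse. The SWEMWBS could then appear to disagree with the DASS-21 in the same women. The Discussion says the study will inform changes to outcome measures for a later trial, so a spurious conflict of this kind could mislead that choice.

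**Working it through.** **1. Direction against stated purpose, row by row (Table 3)**

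| Measure | What the row says it measures | What a higher score is said to mean | Agree? |
|---|---|---|---|
| DASS-21 | levels of depression, anxiety, stress | "Higher the score indicates the more severe the symptoms" | yes |
| SWEMWBS | wellbeing | less wellbeing | **no** |
| MEQ | parental self-efficacy | more self-efficacy | yes |
| PBQ | difficulties in the bond | more perceived difficulty | yes |

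The comparison uses the rationale column, not the scale names. The PBQ shows why: its name suggests bonding, but its rationale says difficulties, and its direction follows the rationale. Only the SWEMWBS row runs against its rationale.

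**2. The stated range**

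Seven items coded 1 to 5 give 7 × 1 = 7 and 7 × 5 = 35, which reproduces the printed range. Coding 0 to 4 would give 0 to 28. The range is therefore sound, but it cannot settle the direction: a reversed total would be 42 − x, which also runs from 7 to 35. The contradiction lies only in the interpretation text.

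**3. What the direction does to the reliable change index**

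Section 2.11 states neither the formula nor the cut-off. I assume the common form, RCI = (post − pre) / (SD × √(2(1 − r))), with a cut-off of ±1.96. The reliability r = 0.86 is from Table 3.

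- √(2 × (1 − 0.86)) = √0.28 = 0.529
- Threshold = 1.96 × 0.529 = 1.04 baseline SD

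The article gives no SWEMWBS standard deviation. Over an assumed range:

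| Assumed baseline SD | Threshold (points) |
|---|---|
| 3 | 3.11 |
| 4 | 4.15 |
| 5 | 5.19 |
| 6 | 6.22 |

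These thresholds are the same in either direction; only the label changes. For example, with SD 4, a rise from 18 to 23 gives RCI = 5 / (4 × 0.529) = +2.36, a reliable improvement if higher is better. Under the printed direction the same woman is reliably worse.

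**4. Illustration for a whole sample**

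This is one simulated set. Only n = 30 comes from the article (the minimum in section 2.5). The rest is assumed: baseline mean 19, baseline SD 4, mean change +2, SD of change 3.

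| Quantity | Higher = higher wellbeing | Printed direction |
|---|---|---|
| Reliably improved | 6 | 0 |
| Reliably deteriorated | 0 | 6 |
| Paired t | +3.81 | −3.81 |
| Paired t, two-sided p | 0.0007 | 0.0007 |
| Wilcoxon, two-sided p | 0.0006 | 0.0006 |

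The p-values are identical, so nothing in the test output would expose the error.

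**The case against.** The strongest reply is that this may be only a slip in an overview table. Section 2.11 does not send the analyst to Table 3 for scoring, and the team may well score from the instrument's own key. In that case no result changes. This stands: the consequence is conditional. A reader might infer that the study will report improved wellbeing as deterioration, but the article does not show that the analysis uses the printed direction.

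A reader might also infer that a false deterioration would affect progression or safety decisions. The article does not support that either. Table 2 has two indicators, recruitment and retention, and the SWEMWBS enters neither. The sample size in section 2.5 does not depend on it. Section 2.10 relies mainly on self-report and the team's routine assessments to identify adverse events, and sets no SWEMWBS threshold.

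Third, the scoring key is a cited source that is not at hand. The case therefore rests on the row's rationale, the lack of any stated recoding and the pattern of the other rows. That establishes a contradiction within the document. It does not exclude a deliberate but undeclared reversal, so the remedy must allow for one.

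Finally, the 1.04 SD figure depends on an assumed formula and cut-off, and it does not measure the harm, because the threshold is the same in both directions. That is correct; the size of the problem is the swap of labels.

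None of this makes the printed line right. It is a positive statement of how a named outcome is to be interpreted, not a detail left to a fuller document.

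**Conclusion.** The point holds in a limited form. The SWEMWBS row contradicts itself on the evidence of the article alone. If ordinary totals are interpreted as Table 3 says, the sign of every non-zero SWEMWBS change is misread and the two reliable change counts swap. If the team scores and reads the scale from its own key, or has deliberately reversed it and reads the reversed score consistently, the results are unaffected and only the published description is wrong or incomplete.

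Severity is moderate: an internal error in the definition of an exploratory outcome in an uncontrolled feasibility study. The swap itself follows from the sign alone and needs no assumption. The point thresholds and the counts of 6 and 0 rest on the assumed standard deviations, reliable change formula, cut-off and simulated change.

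**What to change.** Correct the SWEMWBS row of Table 3 to say that higher scores indicate higher wellbeing. If the scores are deliberately reversed, say so and give the recoding (for a 7 to 35 total, 42 minus the score).

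Check the Qualtrics scoring and the reliable change code against the instrument's scoring key. Recruitment began in May 2025, so some data may already be scored; the check should cover those scores and be finished before the pre-post analysis.

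The cost is one line of text and a short check of the scoring code. No change to the design, the sample size or the planned tests is needed.

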**Figure 2 f2:**
[figure not shown]
SPIRIT figure for the study.

Participants will be encouraged and reminded to complete the follow-up questionnaires via email, text message and phone call, and asked if they would prefer to complete the measures with the assistance of a researcher. All data will be pseudonymised and entered into a database, stored on a secure server, by the research assistant and checked for accuracy and quality by the joint project managers.

### Safety considerations

2.10

Adverse events will be monitored and reported throughout the study in line with sponsor and site reporting systems. A log of all adverse events will record all unexpected adverse events as well as reports of significant or sustained deterioration in the mental health of the participant caused by the intervention during the trial period (date of first contact to final contact). Any such deteriorations will be designated serious adverse events for the purposes of this study, even when hospitalisation is not required. Adverse events will primarily be self-reported to the research team or identified by the research team as part of their routine assessments. Enquiries about adverse events will be made by the project managers. The research team will determine if the event qualifies for expedited reporting. The intervention is low risk and we do not anticipate stopping the study; however, in the unlikely event that any serious adverse events are attributed to participation in the study, the study will be stopped.

We will inform any participant’s General Practitioner (GP) or family doctor of her participation as well as the named perinatal mental health practitioner (e.g., a Case Manager or a Clinical Psychologist) so that they are aware of the participant taking part in the study. Participants are also informed before providing consent and at the time of formal consenting that if they disclose information to the study team suggesting that either the participant or someone else is at risk of harm, the study team may have to inform authorities, such as the participant’s GP or the police. The participant will be involved in the decision as much as possible.

The research team is trained in adult and child safeguarding and in risk and distress management in perinatal mental health and parenting research contexts. The team has conducted a written risk assessment for the study and developed a Sponsor and Trust approved protocol for managing risk and distress before, during and after participant contact to ensure duty of care towards participants. If a researcher observes potential signs of mental health deterioration, the observation will be shared with the participant’s named mental health practitioner and GP. If the participant is assessed to pose an imminent risk to either herself or to someone else, the risk will be discussed with the Chief Investigator (who is also a registered Perinatal Clinical Psychologist) and, if considered appropriate, the researcher will contact emergency services.

Participants may continue to access the intervention for up to 12 months after registration if they so wish. This means participants can access supplementary aftercare in addition to usual care they are already accessing or entitled to via the perinatal mental health service.

### Data analysis

2.11

Participant flow through the study will be reported using the CONSORT diagram (**Figure 1**). Descriptive summaries will be produced for feasibility and other outcome data (e.g., means and standard deviations or numbers and percentages, including percentages and patterns of missing data). We will use a paired t-test or Wilcoxon signed rank test for pre- and post-intervention questionnaire data and the reliable change index (80, 81) to explore changes in clinical outcomes (i.e., potential intervention benefits). However, given that this is an uncontrolled study, any results in relation to outcomes will be treated with extreme caution.

All interview data will be digitally recorded, transcribed verbatim and then analysed using Framework Analysis (82, 83). Informed by the acceptability of healthcare interventions theoretical framework (74), an initial coding framework will be developed to reflect key service and service user-determined topics covered by the interview schedule. Following data familiarisation, this framework will be augmented to encompass new emerging themes. Initially, a subset of transcripts will be coded independently by a member of the research team, and findings will be discussed by the rest of the research team and the PPIE group to develop a shared theoretical framework. This framework will then be applied to the remaining transcripts. Data will be interpreted and analysed within the final framework to structure and compare participant and staff views about the study and intervention. The trustworthiness of the final analysis will be enhanced through the integration of data from different stakeholders and through researcher triangulation.

Given the small-scale uncontrolled nature of this trial, a data monitoring committee was not deemed necessary. Instead, the research team conducted monthly trial monitoring meetings, and the project managers regularly conducted a review of trial documents.

